At baseline, 6 months, and 12 months, the participant will receive a letter via e-Boks (a trusted Nordic provider of secure platforms and digital post boxes) containing a link to a questionnaire. The complete questionnaire battery, consisting of 45 items, is primarily composed of various standardized and validated instruments. For constructs where no validated questions were available, the research team has developed original items. These have been pilot-tested and revised accordingly before being included in the final questionnaire battery. The questionnaire battery covers topics including education level, physical activity, smoking habits, alcohol use, dietary habits, work ability (inspired by WPAI (Work Productivity and Activity Impairment Questionnaire [28])), general health (EQ-5D-5L and EQ-VAS [29]), mental well-being (SWEMWBS (Short Warwick-Edinburgh Mental Well-being scale [30,31])), and e-health literacy (eHLQ [32]-License number: E2019IA). The English version of the complete questionnaire battery is available in Supplementary Material, Table S2.

Much of the data will either be captured electronically or collected during the routine clinical consultations at the GPCs planned as part of the structured management of patients with T2D, thus minimizing the risk of missing data. However, if a GPC forgets to report data, we will have a very close and continuous collaboration with all the participating GPCs giving us the opportunity to make them aware of any forgetfulness. Finally, in case of missing data that cannot be recovered, we will use the “last carrying forward” or “the next carrying backwards” and supplement with sensitivity analyses excluding patients missing the data in focus.

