## 4. Statistics

### 4.1. Power Calculations

In a recent publication using Danish health registries [35], we have calculated that the actual, absolute ten-year risk of cardiovascular disease for the entire DD2 cohort is 12.3%. Generally, 15% relative risk reduction is considered clinically relevant in clinical randomized controlled trials. Therefore, we define the minimal clinically relevant difference as 15% of 12.3%, which is approximately 2%. With a standard deviation of 4%, statistical power set at 90%, and a significance level of 5%, the study will require a sample size of at least 130 patients in both the intervention and the control group. Based on DD2 data [35], we expect approximately 20% of the participants to have prevalent cardiovascular disease and we anticipate 10–15% dropouts, therefore we will include 400 patients in total.

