### 4.2. Analysis

In general, categorical variables will be summarized as numbers (%), continuous variables as min–max, mean (standard deviation, SD), and median (interquartile range, IQR), by randomization group.

The primary analysis of the primary outcome will follow an intention-to-treat principle, but due to the definition of the primary outcome, only participants with relevant measurement available at both baseline and one year of follow-up. We will employ a logistic regression model with robust variance estimation, accounting for GP clustering. As a secondary analysis approach, we will model the count of risk factors at both baseline and at one year of follow-up in a population-averaged longitudinal regression model based on generalized estimation equations (GEE), where group differences are included as a time-by-group interaction term. This approach accounts for clustering and potential missing measurements at each time point and will not be restricted to complete observations.

The analysis of the secondary outcomes will follow these two approaches outlined above. To generate hypotheses, several exploratory post hoc analyses will be conducted. The level for statistical significance is set at 5%. We will use statistical software such as StataBE (version 18.5 or newer) or R (version 4.5.1 or newer) for analysis.

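### The secondary GEE is said to account for missing measurements, but as described it does so only if dropout is unrelated to baseline or acts alike in both arms

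*Protocol article*

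**What the plan says.** All in the protocol article.

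- Section 4.2, primary analysis: intention to treat in principle, but "only participants with relevant measurement available at both baseline and one year of follow-up". The model is a "logistic regression model with robust variance estimation, accounting for GP clustering".
- Section 4.2, secondary approach, outcome: "we will model the count of risk factors at both baseline and at one year of follow-up". The type of model is then described separately: "population-averaged longitudinal regression model based on generalized estimation equations (GEE), where group differences are included as a time-by-group interaction term". Of this model the article says: "This approach accounts for clustering and potential missing measurements at each time point and will not be restricted to complete observations". Both approaches are then carried over to the secondary outcomes.
- Section 4.2 gives no working correlation, weights or missingness assumption for the GEE. The GP clinic is the only clustering unit named, and it is named for the primary model.
- Section 4.1: "we anticipate 10–15% dropouts", with no split by arm.
- Section 2.7: data that cannot be recovered are to be filled by carrying values forward or backwards, and the plan will "supplement with sensitivity analyses excluding patients missing the data in focus".

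**The concern.** The sentence on missing measurements presents a property of the method, not a detail deferred to another document. A GEE with only time, group and their interaction needs dropout to be unrelated to the observed baseline outcome, unless it is weighted or its working correlation ties a patient's 12-month value to that patient's own baseline. If clinic is the only cluster level, neither safeguard is present. All baselines enter the model but only the observed 12-month values do, so the two visits are averaged over different sets of patients.

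The GEE is the model the plan offers against the completers restriction, for the primary and the secondary outcomes, so a reader will take agreement between the two as reassurance about dropout.

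Dropout that differs by arm is plausible from the design:

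- Section 6 has the dietician exclude patients with a suspected eating disorder. Coaches are dieticians (section 2.4), and controls have no coaching in year one (section 2.6).
- Table 1 lists extra visits for unmet risk factors in the intervention arm only.
- Patients and clinics know their arm, and controls are waiting for the intervention.

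**Working it through.** **Reference size.** Section 4.1 sets the target difference as "15% of 12.3%, which is approximately 2" percentage points: 0.15 × 12.3 = 1.845, rounded to 2. The plan gives no figure for bias from dropout, so there is none to reproduce.

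**Inputs from the article.** Overall dropout of 10–15%, SD 4 (section 4.1), 2:3 allocation by clinic (section 2.1), about 70 clinics and 400 patients (section 2.2).

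**Assumptions.** A continuous score stands in for the count of risk factors. SD at each visit is 4 to 6 and within-patient correlation ρ is 0.5 to 0.8. The probability of dropout is logistic in the standardised baseline Z, with slope 1. No weights are used.

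**Formula.** With working independence, the estimated change in an arm is the mean of the observed 12-month values minus the mean of all baselines. Since E[Y₁ | Z] = μ₁ + ρσZ,

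- bias in one arm's change = ρσm, where m = E[Z | retained];
- bias in time-by-group = ρσ(m_intervention − m_control).

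Numerical integration gives m = −0.091 at 10% dropout, −0.112 at 12.5% and −0.133 at 15%. If dropout is unrelated to baseline, m = 0.

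| SD | ρ | Each arm's change, 12.5% in both | Time-by-group, 12.5% in both | Time-by-group, 15% v 10%, slope 1 in both | Time-by-group, 15%, slope 1 in one arm only |
|---|---|---|---|---|---|
| 4 | 0.5 | −0.22 | 0 | 0.08 | 0.27 |
| 4 | 0.8 | −0.36 | 0 | 0.13 | 0.42 |
| 6 | 0.5 | −0.34 | 0 | 0.13 | 0.40 |
| 6 | 0.8 | −0.54 | 0 | 0.20 | 0.64 |

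Time-by-group entries are absolute values. Example: 0.8 × 6 × (0.1326 − 0.0908) = 0.20, and 0.8 × 6 × 0.1326 = 0.64. The sign depends on which arm loses more high-risk patients. If it is the intervention arm, the bias favours the intervention.

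**Check by simulation.** 2,000 trials per scenario: 70 clinics of 6 patients, 28:42, SD 4, clinic ICC 0.05 (assumed), true effect −2. Entries are absolute time-by-group bias.

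| Scenario | ρ | Clinic, independence | Clinic, exchangeable | Patient, exchangeable |
|---|---|---|---|---|
| 12.5% in both, slope 1 | 0.5 | 0.01 | 0.01 | 0.01 |
| 12.5% in both, slope 1 | 0.8 | 0.01 | 0.01 | 0.01 |
| 15% v 10%, slope 1 in both | 0.5 | 0.08 | 0.07 | 0.00 |
| 15% v 10%, slope 1 in both | 0.8 | 0.14 | 0.13 | 0.01 |
| 15% in both, slope 1 in intervention only | 0.5 | 0.28 | 0.24 | 0.02 |
| 15% in both, slope 1 in intervention only | 0.8 | 0.41 | 0.37 | 0.01 |

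Monte Carlo error is about 0.01. An exchangeable correlation at clinic level removes little of the bias. Modelling the correlation within patient brings it to 0.023 or less throughout, without weights.

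**Against completers.** A completers' change score has bias (ρ − 1)σ(m_intervention − m_control). With SD 4 and the one-arm pattern this is 0.27 at ρ = 0.5, the same size as the GEE with opposite sign, and 0.11 at ρ = 0.8, against 0.42 for the GEE.

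**The case against.** The strongest reply is that the article does not say the GEE is unweighted or clustered on clinic alone. It calls the model longitudinal, and working correlation and weights are commonly left to an analysis plan, which is not shown here. That choice decides the result, because a patient-level exchangeable GEE was nearly unbiased in every scenario. This stands: it cannot be said that the planned GEE will be biased. What remains is that the article credits the approach with a property that depends entirely on a choice it does not state.

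Four stronger readings are tempting, and the document does not support them.

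- *Any dropout that depends on baseline risk biases the treatment effect.* It biases each arm's change, but with the same mechanism in both arms the time-by-group term is unaffected in the linear model. (On a log-link count scale the cancellation need not be exact.) The article gives no dropout by arm.
- *The bias is a known fraction of the 2-point target.* The GEE as written models a count of risk factors, not SCORE2-Diabetes. On an assumed five-factor count with a log link, the one-arm pattern gave a spurious rate ratio of 0.97–0.98 under no effect: the same mechanism, of modest size.
- *The GEE is worse than the completers analysis it supplements.* Against a completers' change score that needs a within-patient correlation above 0.5. The plan contains no baseline-adjusted completers model to compare with; its stated primary model is logistic.
- *The GEE is the only analysis that keeps dropouts.* Section 2.7 has a carry-forward/backward rule. If it is applied before the GEE, dropouts are filled in and the problem becomes a different one. The article does not say how that rule fits with section 4.2.

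**Conclusion.** The point holds in a conditional form. Including all available observations does not account for missing data, so the sentence in section 4.2 claims more than the method as described can deliver. With clinic as the only cluster level and no weights, the time-by-group effect is biased when the dropout rate or its dependence on baseline differs by arm, and not otherwise.

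Under the stated assumptions the bias is 4–10% of the 2-point target with 15% against 10% dropout (0.08/2 to 0.20/2), and 13–32% when only one arm's dropout depends on baseline (0.27/2 to 0.64/2). The slope, the correlation, SD values above 4 and the split of dropout by arm are assumptions, and the scale is not that of the GEE as written. The direction of the argument is firm; the sizes are indicative. This should be corrected before analysis, but it does not show that the trial's result will be wrong.

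**What to change.** 1. Delete the claim about missing measurements in section 4.2, or qualify it by stating the missingness assumption on which the analysis relies.
2. Use a longitudinal model that links each patient's two visits within clinic. Any of these would serve:
   - for SCORE2-Diabetes and the continuous secondary outcomes, a linear mixed model with random intercepts for clinic and for patient within clinic, a common baseline mean across arms, and time-by-group as the effect;
   - a GEE with patient-level working correlation and variance made robust at clinic level, which keeps the planned method;
   - multiple imputation by arm, using baseline outcome and clinic, before the GEE.
3. Name the outcome to which each model applies, since the GEE is now written for a count of risk factors.
4. Reconcile section 2.7 with section 4.2: say which analyses, if any, use carried values, and how these relate to the completers restriction and the all-observations model.

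The mixed model and the imputation rest on missing at random and correct specification. The GEE with patient-level correlation came close to the same protection in the two-visit linear case checked here, but has no general guarantee. None of them protects against dropout that depends on the unobserved 12-month value.

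The cost is analysis wording only. The models are standard in Stata and R, which the plan already names, and no new data are needed.

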## 5. Prospects and Potential for Upscaling

It is anticipated that DICTA will enhance the quality of care for individuals with T2D, promote positive lifestyle modifications, and be economically viable for society while reducing disparities in healthcare by improving the care of the most vulnerable and frail among individuals with T2D. Improved lifestyle has been demonstrated to positively impact the symptoms and prognosis of numerous other chronic diseases, including COPD, osteoarthritis, and hypertension. Consequently, it is anticipated that this will have a favorable influence on multi-morbidity. If effective, the intervention could be scaled up nationally through a collaboration between multiple Steno Diabetes Centres, universities, and GPCs. Moreover, the intervention has the potential to serve as a model for the management of other major chronic diseases in Denmark, with only minor program modifications. In the long term, the potential exists for international expansion of the DICTA study together with Compugroup Medical GmBh, Cambio Systems A/S, and Liva Healthcare A/S that are dominant players for digital patient and GP decision support in Northern Europe. Given the strong integration of CDS tools in Danish general practice and the centralized digital health infrastructure, generalizability to countries with less standardized systems may be constrained. Wider implementation would require contextual adaptation to local electronic health record systems, clinical workflows, and policy environments. Nonetheless, the conceptual model underlying DICTA—risk-based CDS combined with patient-centered digital engagement—remains broadly applicable and could be transferred with appropriate co-design and implementation planning. However, several factors must be considered when planning for national or international upscaling. First, variability in technology literacy among patients may influence both engagement and outcomes, particularly among older adults, individuals with lower educational attainment, or those with cognitive impairments. Second, differential levels of digital engagement, ranging from high interaction to minimal usage, could affect the intervention’s consistency and effectiveness across patient groups. Third, adherence and dropout rates may vary significantly in real-world settings without the structure and support of a research context. These challenges highlight the need for adaptive strategies, such as enhanced onboarding, digital literacy support, and continuous user feedback, to optimize equitable access and sustained impact at scale.

## 6. Ethics

The Regional Ethical Committee has approved the DICTA-RCT study (S-20190121) according to Danish law. The management and storage of participant data are being carried out in accordance with guidelines established by the Danish Data Protection Agency. The study has been duly registered and approved by Clinicaltrials.gov: NCT04880005.

There are no inherent risks to health and well-being associated with the engagement in the project. However, the potential for harm exists in the form of the development of eating disorders. Therefore, the dietician is directing particular attention to this matter and will exclude any patient if an eating disorder is suspected. Prior to enrollment, participants will be furnished with a comprehensive explanation of the study in both written and oral formats. Participation in the study and the database is voluntary, and individuals may withdraw at any time. The project has obtained permission from the Danish Data Protection Agency to store the data, and the data will be handled in accordance with the General Data Protection Regulation (GDPR). The Data Protection Officer at Steno Diabetes Center Odense and at Liva Healthcare will ensure protection and monitor data management, ensuring that it is in line with the established rules and regulations. Most of the study data will be securely stored within the Open Patient Data Explorative Network (OPEN) (https://open.rsyd.dk (accessed 25 June 2025), a custom-designed research database provided by the University of Southern Denmark. OPEN adheres to stringent requirements for data logging, password protection, and regular data backups, ensuring compliance with national legislation and protection against unauthorized access. Handwritten data and hard-copy source documents will be securely stored, protected against unauthorized access, and kept under lock, with access limited to authorized personnel only. The REDCap data collection system (Vanderbilt University, Nashville, TN, USA) will be utilized to manage the electronic reporting of source data, in accordance with established good clinical practice standards. During the GP examination, measurements will be entered directly into REDCap, where GPC will be responsible for filling out a designated questionnaire. Access to REDCap will be granted to GPCs via a link to a secure login page. Liva Healthcare is in compliance with GDPR.

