## 2. Materials and Methods

### 2.1. Study Design

The DICTA study is a two-arm, cluster-randomized controlled trial (RCT) and will be conducted across multiple general practitioner clinics (GPCs) in Denmark. A randomization list will be generated using the program “sealedenvelope”, and cluster-randomization will occur at the GPC level, with an allocation ratio of 2:3 (intervention: control) and variable block sizes of 5 and 10 to ensure the balance between the two groups. Our allocation ratio of 2:3 is chosen based on an expectation that recruiting patients into the control group will be more challenging due to lower engagement incentives. Stratification will be based on two factors to ensure equal quality of care and no change in information sharing between study groups. Firstly, the GPC’s participation in the “Specialist supervised individualised multifactorial treatment of new clinically diagnosed type 2 diabetes in general practice (IDA): a prospective controlled multicentre open-label intervention study” [25] will be taken into consideration. Secondly, the physical address of the GPC will be considered. This is because some GPCs share address and health staff, and other GPCs operate as solo practices and thereby reduce the risk of intervention-based guidance of the control group patients. Other aspects such as age and gender of GPs, have not been taken into account as differences in quality of care is small and it is not possible to stratify on this. In Figure 1, the overview of the study’s elements is illustrated for both the intervention and control groups.

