### 2.2. Population and Recruitment

A total of 400 individuals will be recruited through approximately 70 GPCs. Only clinics using the XMO electronic patient journal (EPJ) from CompuGroup Medical Denmark A/S will be eligible. To participate, GPCs must agree to integrate both the CDS tool and the LIVA e-health lifestyle coaching application into their EPJ system for management of T2D.

Eligible patients will be identified through the Danish Centre for Strategic Research in Type 2 Diabetes (DD2). The DD2 and GPCs will jointly facilitate the distribution of written and oral information about the DD2 and the DICTA study. Patients expressing interest will be contacted via email and telephone by a study team member within one to two weeks to confirm eligibility.

The inclusion criteria of the DICTA study are as follows: age between 18 and 80 years, T2D for less than five years (since diagnosis) or no other glucose-lowering medication than Metformin, HbA1c ≥ 53 mmol/mole (changed to 48 mmol/mole and approved by Ethics Committee at 13 July 2023), participation in DD2 and DICTA by the patient’s GPCs, possession of a smartphone, and no previous use of digital coaching via LIVA. The following criteria will be used to exclude patients from the study: participation in other clinical health-related trials, presence of serious or life-threatening disease, cognitive impairment, diseases such as dementia or diseases inhibiting communication, pregnancy, or active pursuance of the same, suspicion of eating disorder, or insufficient Danish language proficiency.

Recruitment commenced in May 2021 and is expected to continue until 400 patients have consented to participate and initiated their involvement in the study. Figure 2 illustrates the expected patient flow in the DICTA RCT study. To keep up the inclusion rate, we planned from the start to continuously encourage GPCs from DD2 to join the study and to encourage participating GPCs to include more patients. Despite that, the inclusion rate was not as high as expected partly because of difficulties in meeting the initial inclusion criteria of HbA1c ≥ 53 mmol/mole because many of the patients were started early on Metformin, reducing HbA1c below 53 mmol/mole before inclusion in the study. Therefore, we reduced the inclusion criteria from HbA1c ≥ 53 mmol/mole to ≥48 mmol/mole in July 2023, which increased the inclusion rate.

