### 2.4. eHealth Lifestyle Coaching

During the intervention, participants receive personalized eHealth lifestyle coaching from a personal health coach via the LIVA app, developed by Liva Healthcare A/S. The health coach will be educated as a dietician and in addition, have completed a 20-h course in digital coaching. At baseline, participants in the intervention group will be provided with instructions for installing the application on their smartphone or tablet, along with a link to schedule their initial virtual meeting with their health coach. If the app is not installed and/or a meeting is not scheduled, Liva Healthcare will proactively contact the participant via email and/or telephone to offer assistance.

Within two to four weeks after the baseline examination, participants will be scheduled for a digital motivational interview with their assigned health coach. Throughout the intervention period, participants receive ongoing, personalized, relationship-driven, asynchronous coaching sessions from the same health coach, fostering a continuous and supportive relationship. These coaching sessions occur on a weekly basis for the first three months of the intervention period, subsequently transitioning to fortnightly intervals for the following nine months.

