### 2.6. Control Group

Participants assigned to the control group will receive usual care during the first year of the study period, in accordance with current Danish guidelines for the management of T2D. This care may include routine consultations with the GPs or other health staff, and all pharmacological treatment decisions will be made independently of the CDS system during this period.

Although the control group participants will not have access to the LIVA lifestyle coaching application or the CDS tool in the first year, they will undergo the same clinical examinations and complete the same questionnaires as those in the intervention group.

After 12 months, participants in the control group will be offered full intervention, mirroring the services and support provided to the intervention group in the first year.

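### The coach may exclude patients with a suspected eating disorder after enrolment, which in year one can happen only in the intervention arm and conflicts with the intention-to-treat principle

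*Protocol article*

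**What the plan says.** Eating disorder appears twice in the protocol article.

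- **At entry (Section 2.2).** The exclusion criteria include "suspicion of eating disorder, or insufficient Danish language proficiency". They apply to all patients, with no distinction by arm, and the sentence that introduces them speaks of excluding patients from the study.
- **During participation (Section 6).** The article names one possible harm: "the potential for harm exists in the form of the development of eating disorders". It then says that "the dietician is directing particular attention to this matter and will exclude any patient if an eating disorder is suspected".

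Three other statements determine how the second rule works.

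- **Section 2.4:** "The health coach will be educated as a dietician". On first contact: "Within two to four weeks after the baseline examination, participants will be scheduled for a digital motivational interview with their assigned health coach". Table 1 puts this contact in week 1–2 after baseline.
- **Section 2.6:** "the control group participants will not have access to the LIVA lifestyle coaching application or the CDS tool in the first year".
- **Section 4.2:** "The primary analysis of the primary outcome will follow an intention-to-treat principle". The same sentence limits the analysis to participants measured at both baseline and one year.

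The article does not say whether a patient excluded under Section 6 leaves coaching, follow-up or the analysis.

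**The concern.** An exclusion applied after enrolment, by the person who delivers the intervention, for something the intervention may bring about, is a different matter from an eligibility criterion. If it operates in one arm only, the patients left in the two arms at 12 months are no longer comparable by design, and intention-to-treat analysis exists to prevent that.

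Reporting of harm is also at stake. The condition that triggers the exclusion is the only harm that the article acknowledges. If patients leave the study on suspicion and are not counted, the report could understate that harm in the arm where it is most likely to arise.

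**Working it through.** The article gives no rate for this event, so there is no figure of its own to reproduce. The check is first one of logic, then of size.

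**1. Does the rule act after allocation and enrolment?** Yes. Section 2.1 randomises clinics in a 2:3 ratio. Section 2.4 gives intervention patients their app instructions at baseline, so the arm is known by then. The first coach meeting comes later, whether one takes the two to four weeks of Section 2.4 or the week 1–2 of Table 1. The rule also answers the *development* of an eating disorder, which entry screening cannot cover.

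**2. Which arm can it reach before month 12?** Only the intervention arm. The coach is the only dietician described. Section 2.6 withholds LIVA from controls in year one, and Table 1 marks coaching onboarding as not applicable for them. Controls are offered coaching after 12 months, when the one-year outcome has already been measured.

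**3. What happens to such a patient in the primary analysis?** If exclusion means leaving the study before month 12, there is no one-year measurement.

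- Under Section 4.2 the patient is not in the primary analysis, without anyone deciding to delete data.
- Under the carry-forward rule of Section 2.7 the baseline value would stand in for the missing one, and the patient would count as unchanged.

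Either consequence of this rule falls on the intervention arm alone.

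**4. How large could the effect be?** Inputs from the article:

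- 400 patients and a 2:3 ratio. If patients divide as clinics do, the intervention arm has 400 × 2/5 = 160.
- Target difference: 15% of 12.3% = 1.845, which the article rounds to 2 points. SD 4 points (Section 4.1).

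Assumptions not in the article: a share *p* of 1 to 5% of intervention patients is excluded, and their mean change in risk differs from that of the rest of the arm by *D* = 2 to 4 points (half to one SD).

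If a share *p* with mean difference *D* is removed, the arm mean shifts by *p × D*.

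| *p* | Patients of 160 | Shift, *D* = 2 | Shift, *D* = 4 | Share of 2-point target |
|---|---|---|---|---|
| 1% | 1.6 | 0.02 | 0.04 | 1–2% |
| 2% | 3.2 | 0.04 | 0.08 | 2–4% |
| 5% | 8.0 | 0.10 | 0.20 | 5–10% |

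**5. Power.** Take 20% prevalent cardiovascular disease and 15% dropout off both arms, following Section 4.1. That leaves 240 × 0.80 × 0.85 = 163 controls and 160 × 0.80 × 0.85 = 108.8 intervention patients. Power for 2 points at SD 4 (two-sided 5%, clustering ignored) is then 0.981, 0.980 and 0.978 at *p* = 1%, 2% and 5%. It barely moves.

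**The case against.** The strongest reply is that Section 6 is an ethics statement and does not define an analysis set. It never says that patients are excluded from follow-up or from analysis, and stopping coaching alone is a possible meaning. Section 4.2 lists no exclusion for suspected eating disorder. On this view there is an ambiguous word and no contradiction. This stands in part: the conflict depends on what exclusion means. But Section 2.2 uses the same verb, for the same condition, to mean exclusion from the study, and Section 6 gives no narrower sense and mentions no continued follow-up.

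A reader might infer three stronger things that the article does not support.

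- *That only the coached arm is screened.* Section 2.2 screens both arms at entry. The asymmetry begins after baseline.
- *That intention-to-treat is certainly broken.* It is not if exclusion is confined to coaching and the 12-month visit is kept.
- *That the named harm vanishes from the data.* Section 2.4 says that interaction on the coaching platform is logged, Table 2 lists visits and hospitalisations from the national patient register, and Section 3 refers to ICD-10 codes in a supplementary table that is not shown. A condensed article may also leave safety recording to the full protocol. All that can be said is that cases may go unreported.

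It is also fair to say that the numbers are few: up to 8 patients, against 16 to 24 of 160 from the anticipated 10–15% dropout. The secondary GEE analysis is not restricted to complete observations. However, it would still have no 12-month value for these patients, and ordinary dropout is not decided by the coach in one arm.

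**Conclusion.** The point holds in a limited form. On its natural reading, Section 6 sets a post-enrolment exclusion that in year one can act only in the intervention arm, on an event that the intervention may cause. Combined with the restriction in Section 4.2 to patients with both measurements, this conflicts with the stated intention-to-treat principle. The conflict rests on reading exclusion as exclusion from the study, which the article suggests but does not spell out.

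The likely effect on the primary estimate is small: 0.02 to 0.20 points, or 1 to 10% of the 2-point target, under the assumed 1 to 5% and a difference of 2 to 4 points. The case for a change therefore rests on keeping the analysis principle intact and on reporting the one acknowledged harm. It does not rest on expected bias in the primary result.

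**What to change.** Reconcile Sections 2.2, 4.2 and 6, and say what exclusion under Section 6 means. Then state that, whatever is decided clinically about coaching, a patient in whom an eating disorder is suspected after enrolment:

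- is invited to the 12-month measurements already planned, where consent allows;
- is analysed in the allocated arm;
- is counted, and the count is reported by arm.

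Add a note to that report that active detection by a coach exists only in the intervention arm during year one, so the two counts are not directly comparable.

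The cost is a few sentences of text and the follow-up of a small number of patients at visits already scheduled. No rule on when coaching should stop is proposed here.
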